### Interventions

Lithium is currently marketed in Italy for the treatment of major depression and it will be prescribed according to Italian usual care. Patients allocated to lithium will be administered an oral starting dose ranging between 150 and 300 milligrams (according to clinical judgement). Suggested final oral dose will have to achieve plasma levels of 0.4 to 1.0 mmol/L. Clinicians will be free of increasing or decreasing the dose according to clinical status and circumstances. Dose changes will be recorded. Following randomisation, treatment is to be taken daily for 1 year unless some clear reason to stop develops. Patients allocated to the lithium arm will receive usual pharmacological and non-pharmacological treatment as clinically indicated. Any other pharmacological treatment will be allowed.

Patients allocated to the control arm will receive usual pharmacological and non-pharmacological treatment as clinically indicated. Patients allocated to the control arm will not be allowed to receive lithium. Any other pharmacological treatment will be allowed.

Routine care outside the trial continues as usual. During the study, participants will be seen as often as clinically indicated with no extra visits required for the trial.

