### Outcomes

Suicide completion and acts of DSH during the 12 months of follow-up will constitute the composite primary outcome. The term “suicide” is defined as an act with a fatal outcome, deliberately initiated and performed by the person with the knowledge or expectation of its fatal outcome. DSH is defined as intentional self-poisoning or self-injury, irrespective of motivation, as the intention to end life may be absent or present to a variable degree [7,8]. To preserve outcome assessor blindness, an independent adjudicating committee (three clinical psychiatrists, with no links to the study and blind to treatment allocation) will anonymously review all deaths and all hazardous acts reported during the 12 months of follow-up by the treating clinicians. The committee will have the role of identifying, among deaths, the cases of suicide, and among hazardous acts those that constitute acts of DSH. Only the cases of suicide and those of DSH validated by the committee will constitute the primary outcome.

As secondary outcomes, we will consider number of events (acts of DSH), number of suicides and all-cause mortality, change in severity of depressive symptoms from baseline to endpoint and adverse reactions during the 12 months of follow-up.

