### Statistical analysis

The statistical analysis will be masked, i.e. the trial biostatistician will be blinded to the treatment groups until the analysis has been completed. All analyses will be performed using Stata/SE, Release 11.1. Data lock will occur at 12 months, when data will be available for all participants. The pattern of missing values will be explored and interactions between treatment group and non-completers/completers will be examined with respect to demographic variables and baseline disease assessment.

The intention-to-treat (ITT) population, consisting of all subject randomly assigned to the competitive treatment strategies, will be used for the analysis of primary and secondary outcomes. Patients with missing values and patients lost during follow-up will contribute to the analysis of the primary and secondary outcomes only for the time during which data are available (censoring). Missing values in depressive symptom ratings will be imputed using the last observation carried forward (LOCF) approach: depressive ratings will be carried forward from the last available assessment to the 12-month follow up assessment. Additionally, patients in each arm will be always analysed according to the corresponding treatment group’s allocation at baseline.

In order to check the consistency of this ITT approach, the primary outcome will then be analysed using a per-protocol (PP) approach. The analysis of the PP population will be used for confirmatory purposes only. If less than 5% of patients switch from the allocated treatment to the competitive treatment, the PP analysis will not be performed.

Kaplan-Meier estimates for the time from randomised treatment assignment until the first event that constitutes the primary outcome will be plotted to compare the treatment’s effect, and log-rank test will be performed to test for differences. A Cox proportional hazard model will be used to explore the effect of possible confounding or interaction factors. Gender and age will be included into the model regardless of statistical significance criteria. The proportional hazard assumption of the effects will be tested. No interim analysis is planned for this trial.

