Time from randomised treatment assignment until all-cause mortality during the 12 months of follow-up will be analysed through a log-rank test for difference in survival between the two groups. The same method will be applied for the following secondary outcomes: suicide mortality, deliberate self-harm. Multivariate analyses will be performed to explore the possible role of prognostic factors on outcomes.

Change in severity of depressive symptoms from baseline to 12 months will be analysed as a continuous variable and as a dichotomous variables, where individuals showing an improvement of al least 50% will be considered treatment responders. Change in severity of illness at 12-months will be compared between the two groups of treatment through appropriate statistical methods for repeated measurements (paired t-test or McNemar non parametric test according to the variables distribution). The number of events/outcomes of interest (suicide or DSH) will be compared between the two groups of treatment through the chi-square test (or the Fisher’s exact test when appropriate). When possible, a multivariate analysis will be performed through a Poisson regression model with a robust error variance.

The proportion of patients with adverse reactions during the study will be compared between the two groups of treatment through the chi-square test (or the Fisher’s exact test when appropriate).

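### Adverse reactions are compared only as a crude proportion by allocated arm; a supplementary analysis by treatment received would cheaply cover non-starters and cross-overs

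*Protocol article*

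**What the plan says.** All the relevant text is in the Protocol article.

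- **Outcomes.** The secondary outcomes include "change in severity of depressive symptoms from baseline to endpoint and adverse reactions during the 12 months of follow-up".
- **Statistical analysis, population.** The intention-to-treat set of all randomised patients "will be used for the analysis of primary and secondary outcomes".
- **Statistical analysis, grouping.** "patients in each arm will be always analysed according to the corresponding treatment" group's allocation at baseline. No exception is made for safety.
- **Statistical analysis, follow-up.** Patients with missing values or lost to follow-up enter the primary and secondary analyses only for the period in which they were observed.
- **Statistical analysis, test.** "The proportion of patients with adverse reactions during the study will be compared between the two groups of treatment", by chi-square or Fisher's exact test.
- **Statistical analysis, departure from intention-to-treat.** To check consistency, "the primary outcome will then be analysed using a per-protocol (PP) approach". No counterpart is given for adverse reactions. "If less than 5% of patients switch from the allocated treatment to the competitive treatment, the PP analysis will not be performed".
- **Interventions.** "Patients allocated to the control arm will not be allowed to receive lithium". A control patient on lithium is therefore a deviation.
- **Background, secondary aim (b).** The aim is long-term tolerability, worded for the augmentation strategy.
- **Baseline and follow up assessments.** Lithium dose and plasma level, concomitant drugs and adverse events are recorded every month.

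**The concern.** For efficacy in a superiority trial, analysis by allocation is cautious: non-adherence pulls the difference toward none and makes a benefit harder to claim. For harm the same pull works the other way. Lithium-arm patients who never take a dose stay in the lithium denominator, and reactions to lithium in controls who take it are counted in the control arm. The difference in reactions then shrinks and is less likely to be detected.

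The article gives efficacy a second look for departures from allocation but gives tolerability none, although tolerability is a stated aim. At stake is whether the trial can report how often reactions occur in patients who actually take lithium, beside the comparison of the two strategies.

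A second, smaller point concerns follow-up time. A crude proportion gives a patient observed for 2 months the same weight as one observed for 12, which does not fit the article's own observed-time rule.

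**Working it through.** **Does the text fix the choice?** Adverse reactions are listed as a secondary outcome. Secondary outcomes use the intention-to-treat set. Grouping is always by baseline allocation. The named test compares the proportion of patients between the two groups. The per-protocol analysis is confined to the primary outcome. Read together, these fix one comparison, by allocated arm. It is a stated rule and not a silence.

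**Inputs**
- n = 105 per arm (Power analysis and sample size calculation).
- Two-sided 5% level. The document sets this for the log-rank test; using it here is an assumption.
- p1 = reaction risk with lithium, p0 = risk without. Not in the document; assumed.
- a = share of the lithium arm that never starts, c = share of controls that takes lithium. Not in the document; assumed, and taken to be unrelated to reaction risk.

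The plan states no figure on this point, so there is none to reproduce.

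**Dilution**
- Lithium arm: L = (1 - a) p1 + a p0
- Control arm: C = (1 - c) p0 + c p1
- Difference: L - C = (1 - a - c)(p1 - p0)

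**Power.** Normal approximation for two proportions: power = Φ((d - 1.96 se0) / se1), where d = L - C, se0 uses the pooled proportion and se1 the two separate ones.

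With p1 = 40%, p0 = 20%:

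| a | c | L | C | Factor | Difference | Power |
|---|---|---|---|---|---|---|
| 0% | 0% | 40% | 20% | 1.00 | 20 points | 89% |
| 5% | 0% | 39% | 20% | 0.95 | 19 points | 86% |
| 5% | 5% | 39% | 21% | 0.90 | 18 points | 82% |
| 10% | 5% | 38% | 21% | 0.85 | 17 points | 77% |
| 20% | 10% | 36% | 22% | 0.70 | 14 points | 61% |

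Example, fourth row: L = 0.90 × 0.40 + 0.10 × 0.20 = 0.38; C = 0.95 × 0.20 + 0.05 × 0.40 = 0.21; difference 0.17 = 0.85 × 0.20.

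With lower assumed risks, 30% v 15%, the undiluted 15 points (74%) becomes 14.25 points (70%) at 5%/0% and 10.5 points (45%) at 20%/10%.

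**Early stoppers.** The outcome is whether a patient had any reaction during the study. Someone who starts lithium, reacts and stops is already counted as a case in the lithium arm. The factor above therefore covers only never-starters and controls who take lithium.

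**Follow-up time.** The observed-time rule implies weighting by time at risk. A chi-square test on patients with any reaction has no such weighting: 2 months and 12 months each count as one patient, though they differ sixfold in observation time. The two statements do not fit together, whichever way patients are grouped.

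**The case against.** The strongest reply is that allocation is the right grouping here. The trial is pragmatic, the arms are defined as strategies, and aim (b) asks about the tolerability of a strategy. Patients who do not start, or who cross over, are part of the strategy's result, and randomisation protects the comparison. This stands. It means the allocated-arm test should remain and is not an error; what can be added answers a second question, about lithium actually taken.

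A further reply is that this is a condensed article, and exposure tables may sit in a full protocol or analysis plan not shown. That is fair as to extra tables, which the article does not forbid. The point rests on what the article does state: grouping always by allocation, and one test for reactions.

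Three stronger readings are tempting and are not supported:
- **That the plan expects switching of 5% or more.** The 5% figure only decides whether the per-protocol analysis is run. It is a contingency, and lithium is barred in controls.
- **That every early stopper biases the result.** Those who reacted before stopping are already counted.
- **That lithium's harm will be understated overall.** Patients and clinicians are unblinded, and the blinded committee reviews only deaths and hazardous acts. Open-label reporting could raise the reactions recorded on lithium. Non-starting or switching related to reaction risk could also change the simple factor.

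An analysis by treatment received has its own weakness. After early stopping for intolerance, the patients left on lithium are the more tolerant ones, and reactions that emerge after stopping would count as off lithium. On/off rates can therefore also understate harm.

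**Conclusion.** The concern holds as a limited one. The article fixes a single crude comparison of adverse reactions by allocated arm and provides no counterpart by treatment received. That comparison is valid for the strategy question, but it is diluted for the question of lithium taken whenever some patients do not start or some controls take lithium.

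The size cannot be settled from the document. It rests on assumed reaction, non-start and cross-over rates and on non-start and cross-over being unrelated to reaction risk. Under those assumptions the loss ranges from minor (20 to 19 points at 5%/0%) to material (20 to 14 points, and power from 89% to 61%, at 20%/10%). Nothing in the document says which end applies.

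Separately, the crude proportion does not follow the article's observed-time rule for patients lost to follow-up. Both points call for a low-cost improvement; neither makes the planned test invalid.

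**What to change.** Keep the comparison by allocated arm as the main tolerability result. Add a prespecified supplementary analysis by treatment received:

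1. Class a patient as lithium-exposed from the first recorded dose, in either arm, using the monthly dose and concomitant-drug records.
2. Report reactions per patient-month on and off lithium, with a rate ratio. This also takes observed time into account.
3. Show reactions by ever-exposed status beside the rates, because on/off rates can select tolerant patients after early stopping.
4. Report the number in the lithium arm who never started and the number of controls who took lithium, so that readers can judge the dilution.
5. Label the whole analysis as supplementary and not protected by randomisation.

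The cost is one or two extra tables from data already to be collected each month. There are no added visits and no change to the sample size or the primary analysis.

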### Random allocation procedure

Patients will be randomly assigned to one of the two treatment groups with an equal probability of assignment to each treatment (allocation ratio 1:1). A centralised randomisation procedure will be employed. The trial biostatistician will prepare the sequence of treatments randomly permuted in blocks of unequal size. The allocation will be stratified by presence or absence of Axis II diagnosis *(patients with unipolar major depression AND personality disorder vs patients with unipolar major depression WITHOUT personality disorder)* because this variable may have an impact on the study outcomes (see Discussion).The randomisation schedule will be generated using nQuery Advisor, release 7.0. Recruiting physicians will contact an administrator at the World Health Organisation Collaborative Centre for Research and Training in Mental Health and Service Evaluation of the University of Verona who will access a computerised system that will provide, after information on the enrolled participant is entered and inclusion criteria are verified, the patient's identification number and the allocated treatment.

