## Discussion

The results of this study should indicate whether lithium treatment is associated with lower risk of completed suicide and DSH in adult patients with treatment resistant unipolar depression, who recently attempted suicide. At present, evidence is lacking to indicate the most effective forms of pharmacological treatment for depressed patients with recent history of DSH. To answer this question is an important clinical issue, given the size of the DSH population and the risks of subsequent self-harm, including suicide. To our knowledge, this is the first study that will prospectively identify suicidal behaviour as an outcome measure and systematically assess it in a randomised design, recruiting a well-characterised and homogeneous sample of patients with treatment resistant major depression, with a high risk for suicidal behaviour. Moreover, as most meta-analyses of randomised clinical trials have not detected a reduction in number of suicides or suicide attempts in studies of antidepressants or anticonvulsants for mood disorders [24], the prospect of an agent with suicide-preventive properties is bound to have an enormous impact on the development of treatment strategies and clinical guidelines [25].

Designing our study, we aimed at being as close as possible to the real-world clinical setting. The recruiting centres will all be community based psychiatric services, where patients are not selected by diagnosis and are a representative subgroup of the general population. Even though this may enhance the external validity of the study and the generalisability of its findings, the heterogeneity of patient population might be an issue. High rate of DSH is usually found in patients with personality disorders (most of all, borderline disorder). This has clinical implications because patients with Axis II disorder comorbidity are clinically different from patients with major depression alone and borderline personality disorder can confer additional risk for suicidal ideation and DSH [26]. For this reason we stratified the randomisation, in order to have an equal distribution of treatment regimens in the two subgroups.

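### Axis II diagnosis is the only stratification factor at randomisation, but the log-rank test is named without strata and the Cox model guarantees only gender and age

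*Protocol article*

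**What the plan says.** All references are to the protocol article.

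- **Random allocation procedure:** "The allocation will be stratified by presence or absence of Axis II diagnosis". No other stratification factor is named. The reason given is that the factor may bear on the outcomes.
- **Discussion:** self-harm is described as frequent in personality disorder, and "borderline personality disorder can confer additional risk for suicidal ideation and DSH". The purpose of stratifying is restated: "For this reason we stratified the randomisation, in order to have an equal distribution of treatment regimens in the two subgroups".
- **Power analysis and sample size calculation:** 210 patients, 80% power, two-sided 0.05 log-rank test, no strata mentioned.
- **Statistical analysis, primary outcome:** a "log-rank test will be performed to test for differences". Then: "A Cox proportional hazard model will be used to explore the effect of possible confounding or interaction factors", and "Gender and age will be included into the model regardless of statistical significance criteria".
- **Statistical analysis, secondary outcomes:** log-rank tests for death from any cause, suicide and self-harm, plus multivariate analyses of prognostic factors that are not listed.

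Axis II diagnosis is not named as a stratum or covariate anywhere in the Statistical analysis section.

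**The concern.** An analysis should normally follow the randomisation. The one factor judged important enough to stratify on is not carried into the named primary test, and the two covariates protected in the Cox model are not the stratification factor. The words about significance criteria imply that any other covariate, Axis II included, could be dropped on a significance rule.

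Efficiency is at stake. Blocking within strata removes chance imbalance on Axis II. A log-rank variance that ignores the strata takes no credit for this, so it is too large when Axis II is prognostic. The test then rejects too seldom under the null and loses some power under the alternative. Leaving the stratum unnamed also leaves room to choose later between stratified and unstratified, or adjusted and unadjusted, results.

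**Working it through.** **1. The plan's own figure.** Inputs: 35% and 10% at 12 months, 105 per arm, two-sided 0.05, 80% power, 31 events.

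- Under proportional hazards, HR = ln(0.90)/ln(0.65) = 0.245.
- Events needed (Schoenfeld) = 4(1.960 + 0.842)²/(ln 0.245)² = 31.4/1.98, or 16.
- Events expected in 210 patients = 105 × 0.35 + 105 × 0.10 = 47.25.
- Power = Φ(√47.25 × 1.408/2 − 1.960) = Φ(2.88) = 99.8%.

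The stated 210 patients and 31 events therefore do not follow from 35% against 10%. That is a separate matter. Here it means only that at the stated effect there is almost no power to lose. Weaker effects must be assumed to see a loss:

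- HR = ln(0.90)/ln(0.75) = 0.366, written 0.37 below. It corresponds to 25% against 10%; the 25% is not in the article.
- HR = 0.5 with a 35% control rate.

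**2. The two tests.** Let x be 1 for lithium and 0 for control in the patient having each event, and p the lithium share of the risk set at that event. The unstratified statistic is Σ(x − p)/√Σp(1 − p) over all patients. The stratified statistic computes x − p and p(1 − p) within each Axis II stratum, then adds numerators and variances over the two strata.

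**3. Simulation over a grid of Axis II effects.** There were 210 patients, allocated 1:1 in permuted blocks of 4 and 6 within strata (block sizes assumed), with exponential times, censoring at 12 months and no dropout. There were 6,000 runs under the null and 4,000 under each alternative. Axis II prevalence (30% and 50%) and the Axis II hazard ratio are assumptions, as the article gives neither. Ranges below are over prevalence; type I error is also over control rates of 25% and 35%.

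| Axis II HR | Type I error, unstratified | Type I error, stratified |
|---|---|---|
| 1.5 to 2 | 0.044–0.049 | 0.046–0.053 |
| 3 | 0.039–0.046 | 0.046–0.053 |
| 5 | 0.027–0.037 | 0.045–0.052 |

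Power, unstratified then stratified:

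| Axis II HR | 35% control, HR 0.245 | 25% control, HR 0.37 | 35% control, HR 0.5 |
|---|---|---|---|
| 1.5 to 2 | above 99% for both | 82.2–83.2% v 82.6–83.4% | 72–73% v 73–74% |
| 3 | above 99% for both | 81.8–83.3% v 83.2–84.5% | 70–72% v 73–75% |
| 5 | above 99% for both | 80.6–81.2% v 83.6–84.3% | 64–68% v 73–74% |

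Matched by prevalence, the largest gain is 73.2 − 64.1 = 9.1 points (Axis II HR 5, prevalence 30%, treatment HR 0.5). Monte Carlo standard errors are about √(0.05 × 0.95/6000) = 0.003 for type I error and √(0.72 × 0.28/4000) = 0.007 for power near 72%. Both tests used the same simulated data.

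**4. Simulation with stratum rates set directly.** Half the patients have Axis II disorder and the treatment HR is 0.37 (4,000 runs). The implied Axis II HR is ln(1 − higher rate)/ln(1 − lower rate).

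| Control rates by stratum | Implied Axis II HR | Power, unstratified v stratified | Gain |
|---|---|---|---|
| 15% / 35% | 2.7 | 82.4% v 83.4% | 1.0 |
| 10% / 40% | 4.8 | 82.4% v 84.2% | 1.8 |
| 15% / 55% | 4.9 | 93.3% v 95.3% | 2.0 |

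Unstratified type I error was 4.0% at 15%/35%, 2.9% at 15%/55% and 2.1% at 10%/60% (Axis II HR 8.7); stratified it stayed at 4.5–5.0%. A separate run gave about 82% v 84% power and 4.6% v 5.1% type I error at 15%/35%, and 1.8% v 4.4% type I error at 10%/60%. The direction agrees throughout; the 15%/35% difference is small enough to move with simulation error.

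**The case against.** The strongest reply is that this is a condensed article. It says log-rank test and never says unstratified, and a fuller plan could name the strata. That stands for the log-rank test alone: a reader might infer that the protocol prescribes an unstratified test, but the text supports only that no strata are named. The Cox sentence does not rest on silence, because it fixes which covariates are always kept and leaves out the stratification factor. Even so, that model is exploratory, no selection rule is written, and Axis II is an obvious candidate for it and for the multivariate analyses.

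Other points on that side also stand:

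- The article says the factor may affect outcomes. It does not assert that it does, and it gives no stratum event rates.
- A reader might infer that stratifying was wasted. The Discussion gives its purpose as balance between arms within the subgroups, and that is achieved whichever test follows.
- A reader might call the unstratified hazard ratio biased towards 1. Marginal and within-stratum hazard ratios are different estimands, and a marginal one is defensible in a pragmatic trial.
- For suicide and death from any cause, events may be very few. The earlier lithium trial described in the Background had three suicides. Stratifying such tests gains little.

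**Conclusion.** The point holds as a modest matter of efficiency. The plan stratifies on Axis II, names a log-rank test without strata, and does not secure Axis II a place in the Cox model. Run as written, the primary test would be conservative to a degree that depends on how prognostic Axis II is:

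- Axis II HR up to 2: about 1 point of power or less.
- Moderate effect, treatment HR 0.37: about 1 to 2 points. With treatment HR 0.5 and Axis II HR 3, about 3 points.
- Axis II HR 5: about 2 to 4 points at treatment HR 0.37 and about 6 to 9 points at 0.5.
- The stated 35% against 10%: practically nothing.

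The stratum rates, the prevalence and both weaker treatment effects are assumptions. A reader might infer that the mismatch undermines the primary result. It does not: the error lies towards too few rejections, so a positive finding would not be in doubt on this account.

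**What to change.** State in the Statistical analysis section, before unblinding, that the primary log-rank test is stratified by Axis II diagnosis as recorded at randomisation. State also that the Cox model includes Axis II, as a stratum or a covariate, with gender and age regardless of significance. The secondary self-harm log-rank test can follow the same rule. For suicide and all-cause mortality, stratification is optional.

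The cost is about one sentence, with no change in sample size or data collection. In the scenarios simulated, the stratified test kept type I error close to 5% and gave up no power beyond simulation error.

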In 2008, the results of a randomised, placebo-controlled trial focusing on the suicide preventive effects of lithium in patients with suicidal behaviour were published [11]. In this multi-centre trial (the SUPLI Study), patients with a recent history of a suicide attempt were treated double blind with lithium or placebo and followed up for 12 months. Of 167 patients included in the analysis, only 75% had a diagnosis of major depression: 20% of the whole sample had a diagnosis of adjustment disorder and 5% was suffering from dysthymia or related depressive disorders [12]. Survival analysis showed no significant difference of suicidal acts between lithium and placebo-treated individuals (adjusted hazard ratio 0.52; 95% CI 0.18 to 1.43). However, post hoc analysis revealed that all completed suicides had occurred in the placebo group accounting for a significant difference in incidence rates (p=0.049). Lauterbach and colleagues have suggested that lithium may specifically have suicide preventive effects because in their RCT all of the observed suicides occurred in the placebo group and none in the lithium group. However, the overall number of events was very small (all three suicides in the placebo group) and the lithium-treated individuals were at a higher risk as a result of the significant difference in number of previous suicide attempts which is the most reliable predictor for further suicidal behaviour [13]. Moreover, it also seems that the potential antisuicidal effect of lithium was independent from its mood-stabilising effects. Speculations about possible mechanisms of action involving the central serotonin system have been suggested, because lithium is thought to facilitate 5-HT neurotransmission [14] or may exert its antisuicidal effects influencing aggressive and impulsive traits that are linked to serotonergic dysfunction and also involved in the mediation of suicidal behaviour [15,16]. Evidence from this study suggested lithium treatment to be effective in reducing the risk of completed suicide in adult patients with unipolar affective disorders, however no clear cut results were found in terms of DSH (or suicidality) and the heterogeneity in terms of diagnosis of the recruited sample might have acted as an important confounder.

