### Baseline and follow up assessments

Before entering the study, patients will be asked to provide informed consent to participate. The following information will be collected at baseline: sociodemographic and clinical characteristics, diagnosis according to the Mini Neuropsychiatry Interview (MINI) [19], laboratory and electrocardiography (ECG) parameters, severity of illness according to the Quick Inventory Depression Scale (QIDS) [20], a self-rated instruments that has been shown to have good psychometric properties [21]. Detailed information will be gathered on previous DSH acts, as well.

Follow-up data will be obtained each month after random allocation using an electronic form, as follows: any death or DSH, lithium oral dose and plasma level (if applicable), concomitant drug treatments, QIDS scores, adverse events and information on laboratory and ECG parameters.

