### Power analysis and sample size calculation

When we first drafted the study protocol, the sample size calculation was based on data from three antidepressant clinical trials that employed completed and attempted suicide as the primary endpoint [7,8] (for details, see clinicaltrials.gov, ClinicalTrials.gov identifier: NCT00927550). However, the most recently published evidence has shown that the event rate of completed and attempted suicide in patients with unipolar, recurrent depression (with or without Axis II diagnosis) is higher than expected and can be more than 35% at 12 months [22,23]. According to this data, hypothesising that lithium augmentation (experimental group) would show a clinically significant advantage by producing an event rate of 10% [7,8], a sample size of 210 patients (105 in each group) achieves 80% power for a 0.05 level of two-sided log-rank test (31 events expected).

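### The Cox model guarantees adjustment only for gender and age; previous suicide attempts/DSH and the Axis II randomisation stratum are not excluded, but should be fixed in advance

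*Protocol article*

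**What the plan says.** The Statistical analysis section compares time to first suicide or DSH act with Kaplan-Meier curves and a log-rank test. No stratification of that test is mentioned. On modelling it says: "A Cox proportional hazard model will be used to explore the effect of possible confounding or interaction factors". The only covariate rule is the next sentence: "Gender and age will be included into the model regardless of statistical significance criteria". A later paragraph adds multivariate analyses of prognostic factors and names none.

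Three other sections bear on this:

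- **Background.** In discussing the earlier placebo-controlled lithium trial, the authors note that its arms differed significantly in the "number of previous suicide attempts which is the most reliable predictor for further suicidal behaviour".
- **Baseline and follow up assessments.** "Detailed information will be gathered on previous DSH acts, as well".
- **Random allocation procedure.** Allocation is 1:1 and stratified by presence or absence of an Axis II diagnosis, because that variable may affect the outcomes. DSH history is not a stratification factor.

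**The concern.** The plan does state a covariate rule, and the rule fits poorly with the plan's own reasoning. The Background singles out one baseline variable as the strongest predictor and reports that imbalance on it complicated the predecessor trial. The baseline form collects a closely related variable. The model then fixes two different covariates. Saying that gender and age enter whatever their significance makes sense only if other factors have to pass a significance criterion.

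Two things are at stake. First, whether the adjusted hazard ratio accounts for self-harm history or for the randomisation stratum would depend on the data, so a reader could not tell a planned adjustment from a chosen one. Second, leaving out a prognostic covariate costs some power. It also pulls the estimated hazard ratio towards 1, and in a trial that happens to be imbalanced it shifts the estimate. A log-rank test gives no effect size, and this Cox model is the only model named for time to first event, so its content matters.

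**Working it through.** **1. The plan's own figures.** The Power analysis section says that "a sample size of 210 patients (105 in each group) achieves 80% power for a 0.05 level of two-sided log-rank test (31 events expected"). Its control rate is described as "higher than expected and can be more than 35% at 12 months", and the lithium rate is 10%.

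- Implied hazard ratio: ln(0.90)/ln(0.65) = 0.245.
- Events for 80% power (Schoenfeld): 4(1.960 + 0.842)²/(ln 0.245)² ≈ 16.
- Expected events with 105 per arm: 105 × (0.35 + 0.10) ≈ 47.

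The stated 31 events do not reproduce from 35% v 10%. That is a separate matter and the present point does not rest on it. A control rate of 25% comes closer: HR = ln(0.90)/ln(0.75) = 0.366, 31 events give 79.9% power, and 105 × (0.25 + 0.10) ≈ 37 events are expected. The simulation in step 3 uses HR 0.366. The 25% rate is an assumption and does not appear in the protocol.

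**2. Average effect, continuous covariate.** The protocol gives no strength for the predictor, so a range is assumed: log HR 0.3, 0.5 or 0.8 per SD. Other settings: 210 patients, control risk 35%, treatment HR 0.5 (true log HR −0.69), selection at p<0.05, 800 runs per row. The Monte Carlo standard error of a power near 0.7 is √(0.7 × 0.3/800) ≈ 0.016.

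| log HR per SD | Power: left out | Power: forced | Power: selected | Runs keeping covariate | Median log HR: left out / forced |
|---|---|---|---|---|---|
| 0.3 | 0.71 | 0.73 | 0.72 | 57% | −0.70 / −0.71 |
| 0.5 | 0.68 | 0.73 | 0.73 | 96% | −0.67 / −0.70 |
| 0.8 | 0.65 | 0.75 | 0.75 | 100% | −0.63 / −0.71 |

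At a control risk of 20%, the covariate was kept in 40%, 83% and 99% of runs. With no treatment effect, type I error was 0.036 to 0.051 across all variants, so there is no inflation.

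**3. Binary factor, with and without imbalance.** Assumed: 50% prevalence, control risks 15% v 35% by factor level, 105 per arm, true HR 0.366.

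- Imbalance left to chance: power 81.9% unadjusted v 82.9% adjusted, a gain of 1.0 point.
- A 15-point imbalance against lithium: power 71% v 83%. With no true effect, HR 1.14 v 1.00 and rejection 6.7% v 4.9%.
- The same imbalance analysed with Cox models: power 69% unadjusted, 83% forced, 81% selected at p<0.05. Null rejection 6.9%, 5.0% and 5.2%; null HR 1.14, 1.00 and 1.00.
- At the protocol's own 35% v 10% (assumed split 25%/45%, same imbalance): power 98% unadjusted v 99% adjusted.

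**4. How likely that imbalance is.** SE of the difference in proportions: √(2 × 0.5 × 0.5/105) = 0.069. For 15 points against lithium, z = 0.15/0.069 = 2.17, a one-sided probability of about 1.5%. For 10 points or more in either direction, z = 1.45, about 15%.

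**5. Axis II.** No size was calculated for the stratum, since the protocol gives no figure for its prognostic strength. The point there is one of consistency: a factor judged important enough to stratify allocation has no guaranteed place in the log-rank test or the model.

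**The case against.** The strongest reply is that little depends on this model. The primary comparison is the log-rank test, the Cox model is there to explore, and a condensed article may leave a covariate list to a full protocol or analysis plan that is not shown. A strong predictor would usually be selected anyway, and step 3 shows that selection recovers most of the power lost under imbalance. All of this stands, and it limits the size of the point. It does not remove it, because the article states a rule rather than staying silent, and a better rule uses data already collected.

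Three stronger readings are tempting and are not supported.

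- *A reader might infer that DSH history is left out of the model.* It is not forced in, but possible confounders and prognostic factors are explicitly to be examined and nothing excludes it. Selection by significance is itself an inference from one phrase, though the natural one.
- *A reader might infer that the hazard ratio will be biased and type I error inflated.* That holds only given an observed imbalance. A 15-point imbalance against lithium has a probability of about 1.5%, and averaged over randomisation there is no inflation.
- *A reader might infer that the protocol calls previous DSH acts the most reliable predictor.* It says that of suicide attempts. DSH, as the Outcomes section defines it, includes acts without suicidal intent and is wider.

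**Conclusion.** The point holds in a limited form. Only gender and age are guaranteed in the Cox model. Previous suicide attempts or DSH acts, and the Axis II stratum, appear to be left to significance criteria, despite the protocol's own reasons for regarding both as prognostic.

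The expected effect is small: about one power point on average in the binary-factor simulation, and up to about ten points (0.65 v 0.75) if the predictor is strong and left out altogether. Type I error is not inflated on average. The 12-point power loss (71% v 83%) and the null hazard ratio of 1.14 arise only under an uncommon imbalance, and that power loss also rests on a hazard ratio of 0.366 that is not the protocol's. At the protocol's stated rates the same imbalance costs about one point. The factor's strength, its prevalence and the selection threshold are assumptions throughout. The main gain is an adjusted estimate whose content is known before the data are seen.

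**What to change.** Before unblinding, pre-specify one treatment-effect Cox model for the primary outcome:

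- treatment, age, gender and number of previous suicide attempts or DSH acts as forced covariates, with baseline hazards stratified by Axis II;
- a statement of which count is used and how it is coded. Every patient has at least one DSH act by inclusion criterion (b), so the logarithm of the DSH count, or 1 v 2 or more, is workable. A count of suicide attempts can be zero and needs another coding;
- no significance-based selection in this model.

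Report its hazard ratio and 95% CI beside the log-rank test, and stratify that test by Axis II. Keep any significance-based search among other factors separate and label it exploratory.

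The cost is one or two sentences, no new data and one extra degree of freedom. With four parameters, the stated 31 events give 31/4 ≈ 8 events per parameter, which is adequate for a fixed model of this size but leaves little room for further covariates.
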